**Treatment Plan**:

- Sutent be administered PO QD from days 1 to 28 (see Figure 1)

Figure 1. Treatment Schema

Determine eligibility

**↓**

| **REGISTER** | **Treatment** | Days  1-7 | 8-12 | 13-14 | 15-19 | 20-28 | 29-42 |
| --- | --- | --- | --- | --- | --- | --- | --- |
| XRT |  | X |  | X |  |  |
| Sutent | X | X | X | X | X |  |

**↓**

Additional chemotherapy (as determined by Medical Oncology)

**↓**

Maintenance Sutent (until death or progression) and appropriate follow-up

- Radiation therapy will start on day 8 and will be given to each site for ten fractions
- Fractions must be separated by at least 16 hours
- The MTD of radiation in combination with Sutent will be determined
- Doses of radiation and Sutent will increase as shown in Table 1 in order to determine the MTD of radiation in Gy and Sutent in mg
- The RPTD will be one dose level lower than the MTD. If the MTD is not reached at dose level 5, no further escalation will occur and this will be the RPTD. The RPTD will then be used for future phase II trials.
- Starting day 43, chemotherapy may be given, as determined by the treating medical oncologist.
- Two weeks after completion of any chemotherapy, maintenance Sutent in 6 week cycles (consisting of Sutent 50 mg PO QD weeks 1-4 followed by no treatment weeks 5-6) until progression or death
- If no chemotherapy is planned, maintenance Sutent (as described above) will start on day 43.

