**Table 1: Pre-therapy and weekly checklists during RT and for follow-up**

| Item | Pre-therapy | Week 1 RT | Week 2 RT | Week 3 RT1 | Week 4 RT1 | Follow-up7 |
| --- | --- | --- | --- | --- | --- | --- |
| Inclusion/exclusion criteria | X |  |  |  |  |  |
| History and Physical | X | X | X | X | X | X |
| Informed consent | X |  |  |  |  |  |
| Pathology confirming cancer | X |  |  |  |  |  |
| Documentation of metastatic disease | X |  |  |  |  |  |
| Performance status | X |  |  |  |  |  |
| Adverse effect assessment |  | X | X | X | X | X |
| CT scan of chest/abdomen/pelvis or whole body PET/CT2 | X |  |  |  |  | X8 |
| Bone scan (omit if PET scan performed)2 | X |  |  |  |  | X8,9 |
| Plain X-ray and/or CT and/or MRI of bone abnormality seen on bone scan | X |  |  |  |  | X3 |
| MRI brain | X3 |  |  |  |  | X3 |
| Hematology4 | X | X | X | X | X | X7 |
| Biochemistry5 | X |  |  |  |  | X7 |
| Pregnancy test6 | X |  |  |  |  |  |

1  If applicable

2  The same test should be done throughout therapy and follow-up.

3 If clinically indicated

4  CBC, differential, and platelet count

5  Comprehensive metabolic profile (glucose, sodium, potassium, chloride, carbon dioxide, BUN, creatinine, calcium, total bilirubin, alkaline phosphatase, AST, ALT)

6  For women of child bearing potential, serum hCG

7  Follow-up visits including hematology and biochemistry tests: every 2 weeks for 2 months then every 3 months for 1 year then every 6 months indefinitely

8  Initially 4-6 weeks after completion of radiation therapy to asses response; then every 3 months for first year then every 6 months indefinitely

­9Optional if not previously involved

Abbreviations: CBC= complete blood count, CT= computed tomography, MRI= magnetic resonance imaging

| **TABLE OF CONTENTS** |  |
| --- | --- |

Page

Eligibility Summary 9

Eligibility Checklist 10

1. Objectives 12
2. Introduction/Background 12
3. Trial Schema 15
4. Inclusion Criteria 16
5. Exclusion Criteria 17
6. Criteria for Discontinuation/Withdrawal of Informed Consent 18
7. Treatment Plan – Pre-radiation, Peri-radiation and Post-radiation Assessments 18
8. Treatment Plan – Extracranial Stereotactic Radiation Therapy 21
9. Drug Therapy - Sutent 23
10. Phase I Dose Escalation Rules 26
11. Additional Interventions – Guidelines for Chemotherapy, Surgery and/or Additional Radiation 27
12. Toxicity 27
13. Measurement of Effect 28
14. Biological Correlates 30
15. Adverse Events 31
16. Statistical Considerations 33

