7.3 Supportive Care

- Antiemetics will be ordered at the discretion of the attending physician.
- Mucositis/esophagitis may be ameliorated with sulcrafate or GI cocktail (e.g. Tylenol #3 suspension, bendaryl elixir, Maalox, viscous lidocaine).
- Intravenous hydration is recommended in patients with inadequate oral intake.
- Treatment-related diarrhea will be managed with high-dose loperamide. The recommended dose of loperamide is 4 mg initially (two capsules) then 2 mg after each loose stool, not to exceed 16 mg daily.

7.4 Follow-up checklist: Follow-up visits are to be done every 2 weeks for first 2 months;
 then every 3 months for 1 years; then every 6 months indefinitely

- History and Physical
- Documentation of current medications
- Adverse effect assessment
- CT scan of chest, abdomen, and pelvis (initially 4-6 weeks following completion of radiation therapy to assess response; then every 3 months for first year then every 6 months indefinitely)
- Bone scan (initially 4-6 weeks following completion of radiation therapy to assess response; then every 3 months for first year then every 6 months indefinitely). The bone scan is optional if the patient did not have any evidence of disease on the bone scan upon enrollment into the trial.
- Whole body 18-FDG PET/CT initially 3 months following completion of radiation therapy and every 3 months for the first year and every 6 months thereafter is an acceptable alternative to CT of chest, abdomen and pelvis and bone scan
- Plain X-ray and/or CT and/or MRI of bone abnormality seen on bone scan (if clinically indicated)
- MRI brain if clinically indicated
- Hematology: CBC (hemoglobin, white blood cell count, platelets) with differential
- Biochemistry: Comprehensive metabolic profile (glucose, sodium, potassium, chloride, carbon dioxide, BUN, creatinine, calcium, total bilirubin, alkaline phosphatase, AST, ALT)- (every 3 months for first 2 years then every 6 months indefinitely)
- Tumor markers, if elevated prior to treatment, are recommended
- 18-FDG PET scan every 6 months (optional).

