**11. ADDITIONAL INTERVENTIONS – CHEMOTHERAPY, SURGERY AND/OR ADDITIONAL RADIATION**

11.1 Interventions prior to protocol therapy: If chemotherapy, surgery and/or radiation are recommended by the treating physicians based on the patient’s clinical needs, they may be performed two weeks before or after days 1-28 of protocol therapy.

For instance, a patient with a history of breast cancer status post mastectomy (three years ago) and adjuvant chemotherapy now presents with a solitary brain metastasis, a single lung lesion and two bone lesions. The brain metastasis and lung lesion are both amenable to resection. Subsequently, the patient receives whole brain radiation and taxane based chemotherapy. After chemotherapy, CT of the chest abdomen and pelvis and MRI of the brain reveal no evidence of metastatic disease but bone scan demonstrates residual uptake in the two bone lesions. Two weeks after completion of chemotherapy, the patient is eligible for protocol therapy. The patient will receive Sutent on days 1-28 and extracranial stereotactic radiation on days 8-12 and 15-19 as per protocol. Two weeks after protocol therapy (day 43), the patient may receive additional chemotherapy. After completion of all planned chemotherapy, the patient will start maintenance Sutent. Therefore, all of the chemotherapy, surgery and whole brain radiation are allowed by protocol but are not considered “on protocol therapy”. While all toxicities of these interventions will be documented and recorded, any toxicity resulting from non-protocol therapy will not count as dose-limiting toxicity.

11.2 If patients have documented progression during additional chemotherapy and/or maintenance Sutent, the patient will be taken off protocol. At that time, any necessary intervention (chemotherapy, surgery and/or radiation will be allowed).

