**12. TOXICITY**

- Radiation side effects are limited to the area involved in the treatment field(s). Acute and late toxicity related to radiation therapy include fatigue, nausea and vomiting, myelosuppression, skin erythema, subcutaneous fibrosis, esophagitis, pericarditis, diarrhea, cystitis, proctitis, myelitis, acute radiation pneumonitis, late pulmonary fibrosis, esophageal stricture, liver dysfunction, kidney damage, small bowel obstruction.
- Sutent toxicities are discussed in detail in Section 9.7
- Grade 3-5 non-hematological toxicities (excluding nausea, vomiting, and alopecia) and Grade 4-5 hematological toxicities will be referred to as dose limiting toxicities (DLT).
  - Esophagitis and mucositis are very common side effects with radiation therapy and grade 3 side effects can be seen after palliative courses of radiotherapy. Therefore, grade 3 mucositis or esophagitis lasting ≤ 7 days will not be considered a DLT. If the grade 3 mucositis or esophagitis lasts > 7 days, it will then be considered a DLT.
- All life-threatening Grade 4 and all fatal toxicities (Grade 5) must be reported immediately and evaluated.
- Acute toxicity: Acute side effects are considered as occurring ≤ 30 days from the start of radiation therapy. They will be documented using the NCI Common Terminology Criteria for Adverse Events (CTCAE) version 3.0 (A copy can be downloaded from [http://ctep.info.nih.gov](http://ctep.info.nih.gov/)).
- Late toxicity: Late side effects are considered occurring > 30 days from the start of radiation therapy. They will be evaluated and graded according to the RTOG Late Morbidity Scoring Scale (See Appendix).

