**16. STATISTICAL CONSIDERATIONS**

- Phase I: The primary objectives are to determine the maximum tolerated dose (MTD) and dose limiting toxicity (DLT) of extracranial stereotactic radiation therapy in combination with Sutent when given to all sites of involved disease in patients with metastatic cancer.
- For dose escalation purposes, the major endpoint will be dose-limiting toxicity occurring within 30 days after the start of radiation therapy.
- Dose limiting toxicity is defined as follows: Grade 3-5 non-hematological toxicities (excluding nausea, vomiting, and alopecia) and Grade 4-5 hematological toxicities.
  - Esophagitis and mucositis are very common side effects with radiation therapy and grade 3 side effects can be seen after palliative courses of radiotherapy. Therefore, grade 3 mucositis or esophagitis lasting ≤ 7 days will not be considered a DLT. If the grade 3 mucositis or esophagitis lasts > 7 days, it will then be considered a DLT.
- The MTD for a specific area will be exceeded if 2 or more patients out of 6 (or a third or more) with disease at that site experience DLT at that dose. The dose immediately below will be recommended for further study.
- Phase II: *(Includes 3 to 6 patients from Phase I MTD):* The median progression free survival with optimal chemotherapy alone for the 4 most common tumor types (lung, breast, prostate and colorectal) ranges from 2.2 to 10.6 months, depending on primary tumor site and degree of pretreatment. Therefore, we will assume a median time to progression of 6.4 months (standard deviation 3.2 months) with chemotherapy alone. With 38 patients, this study has 87% power (α=0.05) to detect a 25% increase in time to progression. Also the 2 year freedom from progression is <5% with chemotherapy therapy and this study has 70% power (α=0.05) to demonstrate a 10% absolute increase in 2 year progression-free survival.
  - All patients included in the study will be assessed for response to treatment, even if there are major protocol treatment deviations or if they are ineligible (intent-to-treat population). Criteria described in Section 10 will be used to assign each patient to one of the following response categories: 1) complete response, 2) partial response, 3) stable disease, 4) progressive disease, 5) early death from malignant disease, 6) early death from toxicity, 7) early death because of other cause, or 8) unknown (not assessable, insufficient data).

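### No chemistry is scheduled during radiation and the follow-up chemistry schedules conflict, so laboratory DLTs may be missed in the 30-day window that drives escalation

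*Protocol*

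**What the plan says.** Section 16 of the protocol fixes the phase I endpoint: "For dose escalation purposes, the major endpoint will be dose-limiting toxicity occurring within 30 days after the start of radiation therapy". It defines DLT as "Grade 3-5 non-hematological toxicities (excluding nausea, vomiting, and alopecia) and Grade 4-5 hematological toxicities", with one further exception for grade 3 mucositis or esophagitis of 7 days or less. Laboratory toxicities are not excluded.

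The synopsis Treatment Plan dates the start of radiation: "Radiation therapy will start on day 8 and will be given to each site for ten fractions". The worked example in Section 11 gives the standard course as "extracranial stereotactic radiation on days 8-12 and 15-19 as per protocol". Section 8.1, item 11, allows a split course for patients with 3 to 5 sites, with radiation to day 33 and concurrent Sutent to day 42.

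On laboratory tests:

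- The biochemistry row of the synopsis checklist table (Table 1, pre-therapy and weekly checklists) is marked before therapy and at follow-up. It is blank for all four radiation weeks.
- Section 7.2, the weekly list during treatment, contains a CBC with differential and no metabolic profile.
- Footnote 7 of the checklist table covers follow-up: "Follow-up visits including hematology and biochemistry tests: every 2 weeks for 2 months then every 3 months for 1 year", then every 6 months.
- Section 7.4 keeps the two-weekly visits for the first 2 months but sets biochemistry at "every 3 months for first 2 years then every 6 months indefinitely".

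Section 6 adds that laboratory abnormalities are by default not reported as adverse events. The exceptions are an SAE criterion, discontinuation from the study, or the investigator's insistence.

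**The concern.** The 3+3 rule can act only on DLTs that somebody observes. Hematological DLTs are covered by a weekly CBC. Non-hematological DLTs that show only in the blood, such as a grade 3 rise in bilirubin, transaminases or creatinine, have no matching scheduled test while radiation is given. For the weeks just after radiation, the protocol gives two different answers on whether a test is scheduled.

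If such events occur and are not seen, the error runs in one direction. The observed DLT count is too low, the rule escalates more often than it should, and the dose carried into phase II may be higher than the true toxicity would support. The protocol says there are no clinical data on this combination, so there is no prior experience to offset a gap in ascertainment.

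**Working it through.** The protocol states no figure for this point, so the check is of the calendar, followed by an illustration of the effect on the 3+3 rule.

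**Window.** Radiation starts on day 8; 8 + 30 = 38. DLTs count on days 8 to 38.

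**First follow-up panel.** The origin of follow-up is not stated, so it is counted both from the end of radiation and from the end of concurrent Sutent. Three months is taken as 91 days.

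| Course | Origin | Footnote 7 (+14 days) | In window? | Section 7.4 (+91 days) | In window? |
|---|---|---|---|---|---|
| Standard | Radiation ends, day 19 | day 33 | yes, one (the next is day 47) | day 110 | no |
| Standard | Sutent ends, day 28 | day 42 | no | day 119 | no |
| Split | Radiation ends, day 33 | day 47 | no | day 124 | no |
| Split | Sutent ends, day 42 | day 56 | no | day 133 | no |

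With no panel in the radiation weeks, these are all the scheduled panels after baseline. On these origins there is at most one in the window, 5 days before it closes, and only in the standard course.

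**Effect on escalation.** Under Section 10 the dose rises after 0 of 3 DLTs, or after 1 of 3 followed by none in the next 3:

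P(escalate) = (1 − p)³ + 3p(1 − p)² × (1 − p)³ = (1 − p)³ + 3p(1 − p)⁵

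Let v be the visible DLT rate and l the laboratory-only rate, taken as independent, so that the true rate is p = 1 − (1 − v)(1 − l). Neither rate is in the protocol; v = 20% and the values of l are assumptions. If every laboratory-only DLT is missed, the rule acts on p = 0.20:

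0.80³ + 3(0.20)(0.80⁵) = 0.512 + 0.197 = 0.709

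| Assumed l | True p | P(escalate), all DLTs seen | P(escalate), laboratory DLTs missed |
|---|---|---|---|
| 2% | 0.216 | 0.482 + 0.192 = 0.674 | 0.709 |
| 5% | 0.240 | 0.439 + 0.183 = 0.622 | 0.709 |
| 10% | 0.280 | 0.373 + 0.163 = 0.536 | 0.709 |

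If half of a 10% laboratory-only rate were caught, the rule would act on 1 − 0.80 × 0.95 = 0.24. It would then escalate with probability 0.62, against the correct 0.54.

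**The case against.** A reader might infer that a laboratory DLT is never measured, or that no chemistry is drawn until 3 months after radiation. The protocol does not support that. Footnote 7 schedules two-weekly panels, and a persistent rise would show at a day 33 panel. History, examination and adverse effect assessment are weekly during treatment, and nothing bars chemistry drawn for clinical reasons. The gap is in scheduled collection.

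The panel counts also depend on the unstated origin. Counted from the start of radiation, footnote 7 would give days 22 and 36 (8 + 14 and 8 + 28), both inside the window. The checklist table sets follow-up after the radiation weeks, so this is the less natural reading, but it is not ruled out. Section 10 further requires at least 30 days of follow-up after patients have been treated. If that runs from the end of radiation (day 49 standard, day 63 split), footnote 7 gives two panels before the cohort decision: days 33 and 47, or days 47 and 61. Section 16 nevertheless dates the DLT itself to 30 days from the start of radiation.

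A reader might also take Section 12 as predicting early organ toxicity, because it lists "liver dysfunction, kidney damage". That list mixes acute and late radiation effects and says nothing about onset within 30 days. Section 9.7 describes no hepatic or renal laboratory signal for Sutent, and liver function limits apply at entry. A low laboratory-only rate is therefore plausible.

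Finally, the Section 6 default leaves it unsettled whether a symptomless, transient grade 3 value would count as a DLT at all. More panels alone would not resolve this.

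These points limit the size of the problem and the certainty about it. They do not remove the blank radiation weeks or the conflict between Section 7.4 and footnote 7.

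**Conclusion.** The point holds as a gap in scheduled ascertainment of the phase I primary endpoint. No chemistry is scheduled during radiation, and the two follow-up schedules contradict each other. Counted from the end of radiation, the DLT window contains one scheduled panel at most (footnote 7, standard course, day 33) and none under Section 7.4 or in the split course.

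The bias, if any, is toward escalation, but its size is unknown. On the assumed rates above, the chance of escalating is overstated by about 3 to 17 percentage points (0.709 − 0.674 and 0.709 − 0.536). It would be less where a panel or a clinically prompted test catches some events, and it approaches zero as the laboratory-only rate does. The protocol gives no basis for saying that escalation would in fact be wrong, or by how much. The case for change rests on the low cost of closing the gap.

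**What to change.** - Reconcile Section 7.4 with footnote 7 of the checklist table on the follow-up chemistry interval, and state the day from which follow-up is counted.
- Add the metabolic profile to the weekly blood draw already scheduled during treatment, in both the checklist table and Section 7.2.
- Obtain one panel at the end of the 30-day window, before each cohort decision.
- State either that the Section 6 default on reporting does not remove grade 3-5 laboratory values from the DLT count, or that the DLT definition excludes them.

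The cost is a short amendment and roughly three panels per patient in the standard course (two radiation weeks plus one at the end of the window). In the split course it is up to about five (four weeks plus one). Most can use draws that already take place; the end-of-window panel may need its own.

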**8.** **TREATMENT PLAN – EXTRACRANIAL STEREOTACTIC RADIOTHERAPY**

8.1 Radiotherapy Guidelines

1. All patients must meet radiotherapy inclusion criteria.
2. All patients will undergo CT simulation prior to the first treatment using the appropriate immobilization device**.** Examples are aquaplast mask for head and neck lesions and stereotactic body frame for thoracic and abdominal lesions.
3. All patients will undergo CT based treatment planning.
4. The definition of volumes will be in accordance with the 1993 ICRU Report #50: Prescribing, Recording and Reporting Photon Beam Therapy.
   1. A gross tumor volume (GTV) will be entered for each lesion, based on available imaging data.
   2. A clinical target volume (CTV) will be defined as the GTV plus a margin for microscopic extension.
   3. A planning target volume (PTV) will be determined which will correspond to CTV plus appropriate margin for tumor motion and set-up uncertainty. This generally will be between 3 and 10 mm.
5. The PTV will be treated to the prescribed dose.
6. Normal tissues must be contoured in order to determine dose volume histograms (DVH) include: both lungs (as the total lung volume) minus GTV, spinal cord, liver, kidney, heart, and esophagus.
7. The treatment plan used for each patient will be based on an analysis of the volumetric dose, including dose volume histogram of the PTV and normal structures. Either 3D “forward” planning or “inverse” planning with beamlet intensity modulated treatment planning is allowed.
8. Image guided treatment is mandatory. Method of image guidance will vary by site. Acceptable methods of image guidance include use of bone fusion, implanted fiducial markers or external optical tracking devices. For sites with possible respiratory motion, documentation of degree of tumor motion by using maximum inspiratory, expiratory and free breathing scans is mandatory. Use of an abdominal clamping device and real-time assessment of diaphragmatic motion by using external optical tracking is mandatory. Use of respiratory gating or active breathing control is optional.
9. Custom blocking will be used on all patients.
10. Treatment is to be delivered using a linear accelerator and photon energies ≥ 6 MV.
11. Radiation is to be delivered to each site over 10 fractions separated by at least 16 hours. Up to 5 sites may be treated. **(Added 7/27/06)** For patients with 3 to 5 sites of disease, it may be difficult to treat all sites of disease during one day. For these patients, an acceptable variant is to treat all 2 to 3 sites during days 8 to 19 and to treat the remaining sites on days 20 to 33. For these patients only, concurrent Sutent will continue until day 42.
12. Radiation Doses (Phase I): A phase I escalation of doses will be performed in order to determine in MTD in Gy

Doses of radiation will increase as follows in order to determine the MTD of radiation in combination with Sutent:

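### For staged-radiation patients with no chemotherapy planned, concurrent Sutent ends on day 42 and maintenance is still fixed at day 43, so the 14-day break disappears

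*Protocol*

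**What the plan says.** The standard schedule is in the synopsis (Treatment Plan) and the Section 3 schema. Sutent is taken daily on days 1 to 28, radiation is given on days 8 to 12 and 15 to 19, and days 29 to 42 are blank for both. After that:

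- Without chemotherapy, the synopsis says: "If no chemotherapy is planned, maintenance Sutent (as described above) will start on day 43".
- With chemotherapy, the synopsis says "Starting day 43, chemotherapy may be given, as determined by the treating medical oncologist", and maintenance follows two weeks after chemotherapy ends.
- Each maintenance cycle is "Sutent 50 mg PO QD weeks 1-4 followed by no treatment weeks 5-6".

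Section 8.1, item 11 adds a variant for patients with 3 to 5 sites. Two or three sites are treated on days 8 to 19, and the team may choose "to treat the remaining sites on days 20 to 33". It then states: "For these patients only, concurrent Sutent will continue until day 42".

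Section 9.4 repeats the day 1 to 28 course and the maintenance rule after chemotherapy. It gives no start day for patients without chemotherapy and does not mention the variant. Section 11.1 says of other interventions that "they may be performed two weeks before or after days 1-28 of protocol therapy", and its worked example reads: "Two weeks after protocol therapy (day 43), the patient may receive additional chemotherapy".

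**The concern.** The variant delays the end of radiation and the end of concurrent Sutent but leaves the next step where it was. Day 43 gives a two-week break only if Sutent stops on day 28. For a patient still taking it on day 42, the same calendar day gives no break.

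Elsewhere each 28-day Sutent course is followed by 14 days off: days 29 to 42 on the standard schedule, and weeks 5 to 6 of every maintenance cycle. The patients who lose the break are those with the longest concurrent course. The synopsis wording is directive, and it is the only maintenance rule in the protocol for patients without chemotherapy.

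Two features sharpen this. At dose levels 1 to 3 the daily dose rises to 50 mg at the start of maintenance, and without a break it does so from one day to the next. Also, the hold-and-reduce rules in Section 9.10 are stated to apply only to phase II, so a phase I patient on the variant has only the general provisions for stopping treatment in Section 6.

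**Working it through.** **Inputs**

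- Standard schedule: last radiation day 19, last concurrent Sutent day 28 (synopsis, Section 3).
- Variant: last radiation day 33, last concurrent Sutent day 42 (Section 8.1, item 11).
- Maintenance start without chemotherapy: day 43 (synopsis).
- Maintenance cycle: 28 days on at 50 mg, 14 days off (synopsis, Section 9.4).
- Concurrent dose: 25 mg at level 1, 37.5 mg at levels 2 and 3, 50 mg at levels 4 and 5 (dose-level table).

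**Step 1: reproduce the standard break.** Drug-free days = maintenance start − last concurrent day − 1 = 43 − 28 − 1 = 14. This matches the blank column for days 29 to 42.

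**Step 2: what the variant moves.** Radiation end: 33 − 19 = 14 days later. Concurrent Sutent end: 42 − 28 = 14 days later. Maintenance start: 0 days later.

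**Step 3: the break on the variant.** 43 − 42 − 1 = 0 days. Keeping 14 days requires a start on day 42 + 14 + 1 = 57; check: 57 − 42 − 1 = 14.

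**Step 4: longest run of consecutive dosing days, through the first maintenance cycle**

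| Schedule | Break before maintenance | Longest run |
| --- | --- | --- |
| Standard | 14 days | 28 days |
| Variant as written | 0 days | 42 + 28 = 70 days |
| Variant, day-57 start | 14 days | 42 days |

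**Step 5: exposure on the variant**

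- By day 70, as written: 42 + 28 = 70 dosing days. With a day-57 start: 42 + 14 (days 57 to 70) = 56. The difference is 14 days × 50 mg = 700 mg at every dose level.
- By day 84, as written (days 71 to 84 off): 42 × dose + 28 × 50 mg. With a day-57 start (days 43 to 56 off): the same expression. Both give 2450 mg at level 1, 2975 mg at levels 2 and 3, and 3500 mg at levels 4 and 5.

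**Step 6: step-up at the start of maintenance.** Level 1: 25 to 50 mg. Levels 2 and 3: 37.5 to 50 mg. Levels 4 and 5: no change. The standard schedule has the same step-up, but after 14 days off.

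**Step 7: the toxicity window.** Section 16 says that for dose escalation "the major endpoint will be dose-limiting toxicity occurring within 30 days after the start of radiation therapy". Radiation starts on day 8, so the window closes on day 8 + 30 = 38, before day 43.

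**The case against.** The best defence is that nothing here is strictly contradictory and the intent is plain. Stopping the concurrent course on day 42 and starting maintenance on day 43 can both be done. The day-43 line sits in a synopsis list that describes the standard schedule. Section 11.1 explains day 43 as two weeks after protocol therapy, so a sensible physician would count two weeks from the actual end of treatment. That is a fair account of what was probably meant, and it supports the fix. It does not repair the text. The Section 11.1 sentence is part of an example on the standard schedule, concerns chemotherapy, and equates the interval with day 43; the general rule beside it counts from days 1 to 28. A patient on the variant without chemotherapy has no other written maintenance rule.

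A second objection is that harm is not shown. This stands. The protocol nowhere says that the break is needed for safety or sets a limit on continuous dosing, and it keeps visits every two weeks for the first two months (Section 7.4) and discontinuation for adverse events (Section 6).

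A reader might also infer more than the documents support:

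- *That all patients on the variant lose the break before maintenance.* They do not. Those given chemotherapy start maintenance two weeks after it ends.
- *That the variant as written gives a lasting excess of drug over the corrected schedule.* It runs ahead at day 70 and is level again at day 84.
- *That chemotherapy is forced on the day after the last Sutent dose.* It is only permitted from day 43, and the physician may wait.
- *That dose escalation is compromised.* The Section 16 window closes before the two schedules diverge.

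**Conclusion.** The point holds for a defined subgroup: patients with 3 to 5 sites, treated on the optional staged variant, with no chemotherapy planned. For them the protocol as written removes the drug-free interval before maintenance (14 days to 0) and produces 70 consecutive dosing days, with an overnight increase to 50 mg at levels 1 to 3. The temporary excess is 14 dosing days at day 70, gone by day 84.

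This assumes that the synopsis day applies to patients on the variant, since no other rule does, and that treatment follows the stated days without delay or dose change. The number of such patients is not given and may be very small. The finding is that the schedule drops a break kept elsewhere and gives no reason for doing so; it is not that patients are shown to be endangered. Severity is minor. No power or sample-size figure is affected.

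**What to change.** Add one sentence to Section 8.1, item 11: for patients on the staged variant with no chemotherapy planned, maintenance Sutent starts two weeks after the last concurrent dose, on day 57. Put matching wording in the synopsis Treatment Plan and in Section 9.4. The chemotherapy rule need not change, because it already leaves the timing to the physician. If continuous dosing was in fact intended for these patients, the protocol should say so and give the reason.

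The cost is a short text change in three places and a maintenance start 57 − 43 = 14 days later for this subgroup only.
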